## Abstract

**Background:**

The therapeutic significance of the cervical pessary has been confirmed by several studies. However, the underlying mechanism by which pessaries reduce the risk of a preterm birth remains elusive. The aim of this study is to investigate the hypothesis whether the application of a cervical pessary may stabilize the ectocervical stiffness in order to achieve a cervical arrest.

**Methods:**

This is a prospective, controlled, non-interventional, post-market, monocentric, longitudinal, cohort study in a tertiary maternity hospital to determine ectocervical stiffness and its changes measured before and after placement of a pessary in singleton pregnancies with cervical shortening in the mid trimester. In order to assess reference values for cervical stiffness, we measured also singleton pregnancies with normal cervical length in the same gestational week spectrum. The cervical stiffness measured with the Pregnolia System as the Cervical Stiffness Index (CSI, in mbar) shall be the primary endpoint, whilst patient delivery data (gestational age, mode of delivery and complications) will be the secondary endpoint. In this pilot study, up to 142 subjects will be enrolled to have a total of 120 subjects (estimated dropout rate of 15%) to complete the study; pessary cohort: 60 (up to 71 recruited), control group: 60 (up to 71 recruited).

**Discussion:**

Our hypothesis is that patients with cervical shortening will present with lower CSI values and that pessary placement will be able to stabilize the CSI values through further prevention of cervical remodelling. The measurement of controls with normal cervical length shall serve as a reference.

## Introduction

Preterm birth (PTB) has been consistently implicated in a wide range of health medical conditions affecting neonates and contributed in up to more than a half of overall perinatal mortality [1]. Spontaneous PTB (sPTB) has multiple causes. Different risk factors influence the aetiologies leading to a final pathway that accumulates into the precocious cervical ripening. Known risk factors include maternal factors, such as ethnicity, age, social or economic status as well as patient’s history, such a previous preterm birth [2]. Furthermore, pregnancy characteristics, such as infections [3, 4], multiple gestation, biological and genetic markers play a predominant role in this context. However, the precise underlying mechanisms resulting in a sPTB remain unexplained [5].

The cervical pessary is a circular shaped device with a smaller circumference to enclose the cervix and a wider circumference to fix the device within the vagina of different height in the shape of a dome. The effectiveness of pessary therapy in singleton and twin pregnancies with cervical shortening has been underlined in several trials, especially when it is applied earlier than 20 weeks of gestations and when Instructions For Use (IFU) have been considered during placement and follow-up [6–13].

Several plausible therapeutic mechanisms of action have been proposed. First, one hypothesis describes the mechanical-rotating effect of the pessary on the uterocervical angle resulting in a smaller angle which prevents direct pressure on the membranes covering the internal os of the uterus and cervix itself [14, 15]. Second, the mechanical engagement of the cervix is enforced due to the constraining modality of the device [16]. The mucus plug creates an immunological barrier between the chorioamniotic membrane and the decidua [17]. Although studies have shown beneficial effect of cervical pessary in reducing a preterm birth, the reasons why pessaries might fail to prevent it remain unknown.

Identifying risk factors for sPTB through a detailed obstetric and medical history, gynaecological examination and objective tests such as transvaginal ultrasound measurement of cervical length and biomarkers like fetal fibronectin are crucial for PTB management [18]. An assessment of a cervical softness is an important, however so far very subjective part of an obstetrical clinical examination. Similarly, the Bishop score considers the estimated cervicovaginal angle and is–though being influenced by a high inter- and intraobserver variability–a clinically established method for labour pre-induction, but not for prediction of sPTB [19, 20].

Up to date, there is no clinically established diagnostic tool allowing reliable and reproducible assessment of cervical stiffness in pregnant women [20]. Certain attempts to appraise cervical stiffness with a cervical elastography have been conducted [21]. A novel aspiration technique-based device quantitatively assessing this is the Pregnolia System. Cervical stiffness alterations are reflected by the Cervical Stiffness Index (CSI) [22]. The device quantifies cervical stiffness by measuring the amount of vacuum required to deform cervical tissue. The device was already safely used in more than 1000 women. The device is known to be a safe tool to assess cervical remodelling by the determination of cervical stiffness in a quantitative and objective manner. However, there are no works up to date assessing the impact of the cervical pessary application on cervical stiffness.

This study aims to evaluate whether women with cervical shortening indicated for pessary treatment have *a priori* lower CSI values than controls with normal cervical length. The research also aims to evaluate the impact of the cervical pessary treatment on the measured cervical stiffness, and whether cervical stiffness, or its changes correlate with birth outcome.

## Materials and methods

### Study design

A prospective, non-interventional, post-market, monocentric, longitudinal, cohort study will be held in a tertiary maternity teaching hospital to determine ectocervical stiffness and its changes measured before and after the placement of cervical pessary. Patients with singleton pregnancies and cervical shortening below the 3. percentile according to the reference values of Salomon et al. will be recruited in the pessary cohort. The findings will be correlated with the birth outcome. The study schedule is depicted in Table 1.

**Table 1 pone.0283944.t001:** Study schedule.

Study Assessment	Information	Screening	Baseline	Follow-up	Postpartum
Visit		1	1	2	Medical Record
Time	Before baseline visit	18^+0^–24^+6^	18^+0^–24^+6^	4 weeks after baseline	4–8 weeks after delivery or termination of the pregnancy
Send / Give Patient Information and Informed Consent Form	X				
Informed Consent process and signature		X			
In- /Exclusion Criteria		X			
Speculum to confirm eligibility			X		
Demographics			X		
Obtain surgical, medical, gynaecological and obstetrical history			X		
Listing of concomitant medication			X	X	X
CL and uterocervical angle measurement			X	X	
CSI measurements			X	X	
Discomfort assessment for CSI and pessary placement			X	X only for CSI	
Adverse Events			X	X	X
Collection of information about preterm birth intervention, delivery and related complications, maternal / fetal health, health economics data					X

A gestational age-matched control of pregnancies with no risk factors for spontaneous preterm birth and normal cervical length will be used for comparison of measured cervical stiffness and outcomes. A total of 142 subjects fulfilling the eligibility criteria will be enrolled. Subjects will be recruited to participate in the study between 18^+0^ to 24^+6^ weeks gestation.

Cervical stiffness is measured with a novel CE-marked medical device, the Pregnolia System, developed by Pregnolia AG and based on research conducted by the Swiss Federal Institute of Technology Zurich (ETH) and University Hospital Zurich (USZ) [22].

Participants will continue to receive all routine obstetrical care and indicated interventions. If the woman agrees to participate in the study, additional study assessments will be conducted during the first visit (18^+0^–24^+6^ weeks of gestation) and the follow-up visit (4 weeks later). Procedures at each visit are detailed and explained in Table 2. The participants will be enrolled during the 18^+0^–24^+6^ week of pregnancy and will be in the study until birth or termination of the pregnancy. The pessaries will be removed at 37^+0^ weeks of gestation according to the national guideline for PTB prevention.

**Table 2 pone.0283944.t002:** Procedures at each visit.

Visit #1 at 18^+0^–24^+6^ weeks of gestation
• Confirm inclusion/exclusion criteria are met • Inform consent signature and enrolment to the study • Speculum examination to confirm eligibility (after screening & enrolment) • Obtain demographic data • Obtain surgical, medical, gynaecological and obstetrical history • 3 consecutive TVUS for cervical length and uterocervical angle assessment • 3 consecutive CSI measurements with the Pregnolia System • Discomfort assessment of CSI measurement (for both cohorts) and of pessary placement (for pessary cohort only) • Adverse Events
**Follow-up visit (4 weeks later)**
• 3 consecutive TVUS for cervical length and uterocervical angle assessment • 3 consecutive CSI measurements with the Pregnolia System • Discomfort assessment of CSI measurement • Adverse Events
**In absence of participant–post-partum**
• Collection of interventions and/or treatments during pregnancy to prevent preterm birth, if any • Collection of delivery information (onset of labour, mode of delivery, GA at delivery, date of delivery) and newborn data (e.g. weight) • Collection of health status data of mother (hospitalization (yes/no), indication for hospitalization, GA at admission and GA/date at discharge) and neonatal morbidities. • Collection of health economics (date admission to NICU of the baby, date of discharge from NICU of the baby, discharge from hospital (baby)) • Adverse Events

### Study approval and registration

The ethics committee (Ärztekammer Hamburg, project number 2021-100680-BO-ff) has approved the study (study identifier #4011, protocol version 1.0 of June 9^th^, 2021), and the study has been registered on clinicaltrials.gov (NCT05267717). It is intended that the results of the study will be published as a scientific work. Any modifications to the protocol which may impact on the conduct of the study, potential benefit of the subject or may affect subject safety, including changes of study objectives, study design, patient population, sample sizes, study procedures, or significant administrative aspects will require a formal amendment to the protocol.

### Study population

The study population will consist of pregnant women attending the Asklepios Klinik Barmbek, Hamburg Germany at 18^+0^–24^+6^ gestational weeks for the second trimester scanning. Study eligibility will be determined at the first visit and women can be selected for the study if they meet the inclusion and exclusion criteria described below. Written informed consent is required from all patients included in this study in order to have their data from medical records used in this research project.

Our research will be a longitudinal cohort-study. Hereby, we are planning two cohorts to allow a comparison of the cervical stiffness between the groups: the pessary-cohort consisting of patients with cervical shortening and the control group consisting of patients with normal cervical length (non-pessary cohort).

#### Sample size calculation

In this pilot study, up to 142 subjects will be enrolled to have a total of 120 subjects (estimated dropout rate of 15%) for the study; pessary cohort: 60 (up to 71 recruited), non-pessary cohort: 60 (up to 71 recruited). Currently, it is difficult to perform a formal power analysis since the Pregnolia System is a novel device and there exist only limited clinical data.

#### Inclusion and exclusion criteria

All participants should meet the following inclusion criteria in order to be eligible:

Pregnant woman recruited between 18^+0^–24^+6^ weeks of gestationMaternal age ≥ 18 yearsSubject able to sign approved consent form to participate in the studySingleton gestation

Moreover, there are specific inclusion criteria for both the pessary and the non-pessary cohorts. For the pessary cohort, these consist of cervical shortening confirmed by transvaginal ultrasound (TVUS) (CL < 3^rd^ percentile at gestational age at measurement) according to Salomon at al. (14, 32), whilst for the control (non-pessary) group we will include asymptomatic pregnant women with no risk factors for spontaneous preterm birth and with a normal cervical length.

Any possible exclusion criteria will be evaluated for eligibility for the study on the first visit. Exclusion criteria for both pessary and control group will be:

evidence of fetal anomaly or fetal chromosomal abnormality from fetal scanninguterine malformationshistory of diethylstilboestrol (DES) use, (cases of so-called DES daughters, who were exposed to DES *in utero*)cervical cerclage or pessary currently in placesilicone allergypainful regular contractionsabnormal placentation (previa, accreta)rupture of membranescervical dilationany visible, symptomatic cervical or vaginal infections (this excludes treated, asymptomatic infections)known HIV infectioncervical carcinomathe presence on the cervix at the 12 o’clock position of any of the following conditions: Nabothian cyst, cervical myomas, cervical condylomas, cervical endometriosis, cervical tears, scar tissue, cervical ectopy, cervical scarring due to prior LLETZ, cervical squamous intraepithelial lesion, cervical dysplasia, cone biopsy,vaginal bleeding evident on exam.

#### Criteria for withdrawal

The subjects will be advised in the Informed Consent Form that they have the right to withdraw from the study at any time without prejudice and may be withdrawn at the Investigator’s discretion at any time when this is considered to be in the interest of the subject. In the case that a subject drops out of the study or is withdrawn, the withdrawal / study termination page in a Case Report Form (CRF) shall be completed. On the withdrawal page of the CRF, the investigator should record the date of the withdrawal, the person who initiated withdrawal and the reason for the withdrawal. Reasonable effort should be made to contact any subject lost to follow up during the study in order to complete assessments and retrieve any outstanding data.

Withdrawal can be decided by the investigator due to an adverse event, a major protocol deviation that may lead to endangerment of the subject, a major protocol deviation concerning the primary outcome related to data quality, an investigator’s concern regarding subject’s health and withdrawal of informed consent. Discontinuation due to an Adverse Event should be documented in the CRFs.

### Study device and indication

The Pregnolia System is used to provide information about the mechanical properties of the uterine cervix by assessing the tissue stiffness through a proxy parameter (the Cervical Stiffness Index, in mbar). The system consists of a reusable component, the Pregnolia Control Unit and a disposable probe, the Pregnolia Probe.

The device is intended to be used in addition to other standard examinations and does not substitute them. Cervical stiffness can be assessed during routine examinations—along with other parameters, such as cervical length measured by ultrasound—in order to gather a supportive data for diagnostics in the field of obstetrics and gynaecology, in particular about cervical remodelling.

### Study device description

The Pregnolia System is composed of two products: an active device (Pregnolia Control Unit) and a single-use sterile probe. The Pregnolia system is depicted in Fig 1. The control unit console is an active device with a power supply, foot switch, connector cable and an integrated pump that generates vacuum. The single-use sterile probe is connected to the control unit console through a connector cable. Air filters on the probe prevent microbiological contamination of the control unit. The probe is transvaginally applied on the anterior lip of the cervix with the aid of a speculum and an external light source. A general overview of the system application is shown in Fig 2.

**Fig 1 pone.0283944.g001:**
[figure not shown]
System components: Control unit including control unit console, power supply (not shown), foot switch, connector cable and single-use probe. From the Instructions for Use of the Pregnolia System (www.pregnolia.com/instructions).

**Fig 2 pone.0283944.g002:**
[figure not shown]
General overview of the method and application. The probe is manually placed on the cervix during a routine gynaecological evaluation, with the aid of a speculum. Adapted from [20].

To determine the tissue stiffness, the control unit console generates a weak vacuum, and the cervical tissue is slowly deformed into the probe tip. The vacuum level required to displace the tissue into the probe tip by a fixed distance (4 mm) characterizes the tissue stiffness; it is defined as the Cervical Stiffness Index (CSI) and expressed in mbar. The stiffer the tissue, the higher the closing pressure.

#### Risks / Benefits

The study will be performed on pregnant women. While this study does not have direct impact on the pregnant women, the study results will help to provide better preterm birth management in the future. Pregnant women in emergency clinical settings will not be recruited.

Participants will undergo an additional procedure to quantify cervical stiffness. The study investigator will decide case by case if this additional procedure and the potential risk is acceptable for the pregnant women.

Each subject will undergo one speculum examination for checking the eligibility of the study, 3 consecutive TVUS cervical length and uterocervical angle assessments during two visits (it is an extra measurement only for the non-pessary cohort in the follow-up visit) and 3 consecutive cervical stiffness measurements during two visits.

Speculum examination and TVUS cervical length assessment are standard examinations for pregnant women and no additional risk is associated with this additional examination. The cervical stiffness measurement is done with the Pregnolia system. It has been CE-marked by TÜV Süd. Part of the registration process included a risk-benefit analysis of the Pregnolia system.

The Pregnolia System allows the assessment of cervical stiffness and its monitoring. The system provides an objective, more hygienic and less intrusive way of measuring cervical stiffness than cervical palpation. Possible side effects can be found in the Instruction for Use (IFU). However, the device seems to have a very good safety profile as the manufacturer received no serious adverse event reporting related to the medical device until now, neither in studies nor from the market.

The comparison of the benefits of the Pregnolia system with the risks shows that the benefit outweighs any of the potential risks considering their nature and frequency to prevent them.

### Study objectives

The primary objective is to determine the absolute value of CSI and its change over time in women undergoing pessary treatment, in comparison to normal pregnancies, when measured at 18^+0^ to 24^+6^ weeks and at the follow-up visit (4 weeks later).

The secondary objective is to determine the correlation of the initial CSI and CSI changes with birth outcome (gestational age at birth).

The safety objective is the safety of the device, by assessing incidence, severity, and seriousness of device-related adverse events.

### Study endpoints

The primary endpoint of the study is the Cervical Stiffness Index (CSI, in mbar). The secondary endpoint is patient delivery data (including gestational age, mode of delivery and complications). The safety endpoint is device-related adverse events (incidence, severity, and seriousness).

### Study assessments

The participation in the study will be added to the medical record. Additionally, the access to medical records is needed for the collection of study-relevant data such as previous history of the spontaneous PTB, demographic data, etc.

#### Assessment of primary endpoint

The primary endpoint is assessed via 3 consecutive CSI measurements with the Pregnolia System to obtain the CSI values. During all the visits the CSI measurements with the Pregnolia System are done according to the IFU. Briefly, the Pregnolia Control Unit is set up and one Pregnolia Probe, single use and sterile, is connected to the control unit. The woman is prepared for a speculum-based vaginal examination, excessive mucus is removed, and the measurement site is checked for contraindications / withdrawal criteria. The pump is started, and the probe is gently applied on the cervix at 12 o’clock position. The user is guided through the different steps of the measurement by audio signals. The CSI assessment is performed 3 consecutive times, and thereafter the probe is removed. The results (CSI1, CSI2 and CSI3) are reported in the CRF. The study team will be trained to ensure the right handling of the device.

The measurements should be made consecutively. In case of a measurement failure, this will be recorded in the CRF.

#### Assessment of secondary endpoint

Patient delivery data will be collected in the medical records of the subjects, within 4–8 weeks after birth / study completion. The following information will be collected: a collection of interventions and/or treatments during pregnancy to prevent preterm birth, if any, a collection of delivery information (onset of labour, mode of delivery, GA at delivery, date of delivery) and new-born data (e.g. weight, neonatal morbidities), a collection of health status data of mother (hospitalization (yes/no), indication for hospitalization, gestational age (GA) at admission and GA/date at discharge) and neonatal morbidities, a collection of health economics (date admission to NICU of the neonates, date of discharge from NICU, discharge from hospital).

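### The postpartum record review is timed from birth (4–8 weeks) but must supply discharge dates and neonatal morbidities, so these risk being cut off in the earliest-born infants

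*Protocol article*

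**What the plan says.** Two places in the protocol article set the timing. The Assessment of secondary endpoint section states: "Patient delivery data will be collected in the medical records of the subjects, within 4–8 weeks after birth / study completion". The study schedule (Table 1, under Study design) has a single postpartum column, timed at "4–8 weeks after delivery or termination of the pregnancy".

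The items assigned to that review are of two kinds:

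- **Known at delivery:** onset of labour, mode of delivery, gestational age, date of delivery and birth weight.
- **Dependent on the infant's later course:** neonatal morbidities, within "new-born data (e.g. weight, neonatal morbidities"), and the health-economics dates, "date admission to NICU of the neonates, date of discharge from NICU, discharge from hospital".

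Table 2 repeats this list under its post-partum heading and makes clear that the review is done without the participant present.

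The endpoint is defined as "The secondary endpoint is patient delivery data (including gestational age, mode of delivery and complications"). The secondary objective is narrower: to "determine the correlation of the initial CSI and CSI changes with birth outcome (gestational age at birth"). Under Study design, women "will be in the study until birth or termination of the pregnancy". The article describes no later review and no rule for an infant who has not yet been discharged.

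**The concern.** The review is timed from birth, but some of what it must collect exists only once the infant has gone home or died. The gap between the two is longest for the infants born earliest. Such births can occur here: women enter from 18+0 weeks, and the pessary cohort is selected for a cervical length below the 3rd percentile.

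For an infant still in hospital at the review, the discharge date does not yet exist and later morbidities have not yet been recorded. Whether this happens depends on gestational age at birth, which is the outcome in the secondary objective. If such stays are left blank, the longest drop out of the summary. If they are closed at the review date, they are shortened. In both cases NICU and hospital stay would look shorter than they were, and late complications would be under-counted in the most preterm births. The four-week width of the window adds a smaller problem: for some infants, whether a discharge date is available depends on the week in which the record is opened.

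**Working it through.** **Inputs from the protocol article**

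- Review window: 4 to 8 weeks after birth (Table 1; Assessment of secondary endpoint).
- Enrolment: 18+0 to 24+6 weeks (Study design).
- Planned completers: 60 per cohort (Sample size calculation).

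The window is a schedule entry with no calculation behind it, so there is no figure of the plan's own to reproduce.

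**Input assumed**

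- Postmenstrual age at hospital discharge of a survivor: 35 to 38 weeks. The article gives no discharge age or length of stay.

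**Step 1: who is still in hospital at the review.** A survivor is still in hospital at *w* weeks after birth if gestational age at birth + *w* < discharge age, that is, if gestational age at birth < discharge age − *w*.

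| Assumed discharge age (weeks) | In hospital at 8 weeks if born before | In hospital at 4 weeks if born before |
|---|---|---|
| 35 | 35 − 8 = 27 | 35 − 4 = 31 |
| 36 | 36 − 8 = 28 | 36 − 4 = 32 |
| 37 | 37 − 8 = 29 | 37 − 4 = 33 |
| 38 | 38 − 8 = 30 | 38 − 4 = 34 |

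Below 27 weeks, the result at the 8-week limit is the same over the whole assumed range.

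**Step 2: an example.** An infant born at 24 weeks is reviewed at 24 + 4 = 28 to 24 + 8 = 32 weeks postmenstrual age. The assumed stay is 35 − 24 = 11 to 38 − 24 = 14 weeks. A stay closed at the latest permitted review would be recorded as 8 weeks, which is 3 to 6 weeks too short.

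**Step 3: effect of the window's width.** With discharge at 36 weeks, a survivor born from 28 to below 32 weeks has a discharge date if reviewed at week 8 but not if reviewed at week 4.

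**Step 4: how many infants.** The article gives no rate of very preterm birth. As an illustration only, if 2%, 5% or 10% of the 60 pessary-cohort completers delivered early enough, then 60 × 0.02 = 1.2, 60 × 0.05 = 3 or 60 × 0.10 = 6 stays would be open at the review.

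**Step 5: does the wording supply a later anchor?** The mention of study completion alongside birth might seem to. However, Study design ends participation at birth or termination of the pregnancy, so for an individual woman the two coincide. The monthly updating of case report forms (Data management and confidentiality) is tied to the phases of the study and does not promise an update after the postpartum review.

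**The case against.** The strongest reply is that the main results do not depend on this. The primary endpoint is CSI, and the secondary objective uses gestational age at birth. That age, mode of delivery, onset of labour and birth weight read the same at week 4 and week 8. The NICU dates are labelled as health economics, and no stated objective or named analysis rests on them. All of this stands and limits the scope of the point.

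A second reply is that the source is the medical record, so an open entry can be completed later without recalling anyone, and nothing forbids a second look. This also stands. A reader might infer that discharge dates will be missing for every infant born below the thresholds, but the article does not support that. Re-abstraction is not excluded, a death ends the stay before discharge, and NICU and hospital discharge are separate items, so an infant may leave NICU before going home. The thresholds apply to hospital discharge of survivors, under an age taken from outside the document.

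A third reply is that the handling of open stays belongs in the completion instructions or the analysis plan, neither of which is shown. That is fair for analytical detail, and no fault is found with its absence. The point rests on what the article does state: a window counted from birth, given twice, and applied to items that depend on discharge.

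**Conclusion.** The point holds in limited form. Followed as written, the review can precede hospital discharge of survivors born before about 27–30 weeks (at 8 weeks) or about 31–34 weeks (at 4 weeks), assuming discharge at 35–38 weeks postmenstrual age. Length of stay and late neonatal morbidity are then at risk of censoring or under-recording in a way related to gestational age at birth. Morbidity bears on the secondary endpoint only so far as it counts among the complications named there.

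Two further inferences go beyond the document. One is that nearly all affected infants would be in the pessary cohort. More of them there is plausible, because controls have a normal cervical length and no risk factors, but the article gives no very preterm birth rate for either cohort. The other is that records reviewed at 4 and at 8 weeks are not comparable in general. That applies only to discharge dates and late morbidity, not to the delivery data.

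The number of infants is probably small in a pilot with 60 completers per cohort. The point is minor to moderate.

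**What to change.** Keep the 4–8 week review for maternal and delivery data. Complete the neonatal items (NICU discharge, hospital discharge, morbidities) at the later of that review or the infant's final discharge or death, and say so both in Table 1 and in the Assessment of secondary endpoint section.

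If a fixed cut-off must be kept, add a field recording that the infant was still in hospital, with the date, and treat the stay as censored at that date and not as missing.

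The cost is a second look at the records of a few infants and a slightly later data close for them. No extra visit, recall of participants or change to clinical care is involved.
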